# Impact of a school-based intervention on nutritional education and physical activity in primary public schools in Chile (KIND) programme study protocol: cluster randomised controlled trial

**DOI:** 10.1186/s12889-016-3878-z

**Published:** 2016-12-03

**Keywords:** Childhood obesity, Food education, Healthy kiosk, Physical activity, Schools

## Abstract

**Background:**

Chile has suffered a fast increase in childhood obesity in the last 10 years. As a result, several school programmes have been implemented, however the effectiveness of these needs to be evaluated to identify and prioritize strategies to curve this trend.

**Methods:**

Cluster randomized controlled trial. Twelve primary public schools chosen at random over three regions of the country will take part in this study. The sample size consisted of a total of 1,655 children. For each region one school will be selected for each of the three nutritional intervention modes and one school will be selected as the control group. The intervention modes consist of the following:Healthy Kiosk and nutritional education (KSEAN);Optimized physical activity (AFSO);Healthy Kiosk and nutritional education (KSEAN) + optimized physical activity (AFSO);Control group.

The effectiveness of each intervention will be evaluated by determining the nutritional condition of each child by measuring percentage of body fat, BMI and the z-score of the BMI. This study will also identify the eating behaviours, nutritional knowledge and fitness of each child, along with the effective time of moderate activity during physical education classes.

**Discussion:**

A protocol to evaluate the effectiveness of a school based intervention to control and/or reduce the rates of childhood obesity for children between 6 and 10 years of age was developed. The protocol was developed in line with the Declaration of Helsinski, the Nüremberg Code and the University of Chile Guidelines for ethical committees, and was approved by the INTA, Universidad de Chile ethical committee on Wednesday 12 March 2014.

There is consensus among researchers and health and education personnel that schools are a favourable environment for actions to prevent and/or control childhood obesity. However a lack of evidence on the effectiveness of interventions to date has led some to question the wisdom of allocating resources to programmes. This is the first study of this kind in Chile and could be an important first step to provide guidance to political authorities in relation to which food and nutrition strategies to prioritize to curve this alarming trend.

**Trial registration:**

ISRCTN32136790, registered retrospectively on 05 September 2014.

## Background

Chile has experienced an accelerated process of epidemiologic and nutritional transition. During this process, very rapid changes have taken place, going from a pre-transition condition where infectious maternal and child diseases predominated public health issues during the decade of the 60s, to a post-transitional condition where chronic, non-infectious diseases dominate (ENT) [1]. Studies have identified that this has resulted due to a broader dietary offering, changes in eating patterns and a considerable increase in sedentary behaviours/lifestyle [2, 3].

The Junta de Auxilio Escolar y Becas (JUNAEB), a Chilean government organization, measures the height and weight of all 6-year-old children attending year one of primary school and found that during 2013 the obesity prevalence for this group of children was 25.3% [4].

The World Health Organization (WHO) has indicated that there is convincing evidence that a sedentary lifestyle along with a diet consisting of a high consumption of foods high in calories and deficient in fruits, vegetables, legumes and fat-free dairy products increases the risk of obesity. However, a suitable home and school environment that promotes the choice and consumption of healthy foods could reduce this risk in children [5].

Childhood obesity is one of the main issues affecting public health, not only due to its increased incidence, but also because the obesity is maintained throughout adolescence and adulthood [6–8]. It is associated with a higher risk of cardiovascular diseases [9], diabetes [10], some types of cancer [11, 12], depression [13], discrimination [14] and weight-related problems, as well as other illnesses, where the short- and long-term risks of childhood obesity translate to a decrease in quality of life [15], requiring earlier interventions that result in healthy behaviours within an obesogenic environment [16].

Schools have been identified as a key setting in the reduction or prevention of the prevalence of overweight and obesity [17, 18], as they provide continuous and intensive contact with children during their formative years. The school infrastructure and the physical environment, policies, programmes and staff have great potential to provide a positive influence on the health of children [16]. However, most research has been based on diverse strategies, covering one or more components (nutritional education, reducing time spent in front of the television, providing reading material, modifying the school menu, reducing sedentary behaviours) [19, 20], and has not been able to show convincing results regarding the effectiveness of school-based programmes in reducing overweight and obesity [21].

Even though school-based interventions have been clearly shown to be more effective than interventions in other settings, it has not been demonstrated that interventions consisting of multiple elements are more advantageous than ones consisting of a single element [20, 22, 23]. This has resulted in the growing need to generate high-quality evidence to guide public policymaking in this area.

Since the year 2000, a series of structural and individual initiatives, linked with the promotion of healthy lifestyles to prevent obesity in the population, have been promoted in Chile. These initiatives have implemented programmes to promote healthy lifestyles in schools, such as VIDA CHILE [24] and the Global Strategy against Obesity (EGO-CHILE) [25]. Additionally, in 2012, the National Education Council approved changes to the school curriculum that increased the number of hours dedicated to physical activity in schools to 3 or 4 hours per week, and promulgated a new law, the “Ley de Composición Nutricional de los Alimentos y su Publicidad”, which prohibits the marketing/advertising and the sale inside schools of foods high in calories, saturated fats, sugars and sodium to children under the age of 14 years﻿ [26].

The KIND study looks at addressing the deficiencies of previous studies and as such should enable evaluation of the effectiveness of an integral school-based intervention in diet and physical activity. The study is aimed at controlling the increase in obesity in children aged between 6 and 10 years, from a medium-low and low socio-economic status, that attend public schools. This study will be conducted in three regions of the country and will provide valuable information that should enable the development of an integral view of the dietary and nutritional status of children attending public schools in Chile.

## Methods

### Design

The proposed study is a cluster randomized controlled trial to evaluate the effect of a school-based intervention in nutritional education and physical activity over two school years in children aged between 6 and 10 years, attending primary public schools. Three modes of intervention will be implemented and the results will be measured alongside those of a control group. The intervention modes consist of the following:Intervention 1: Healthy Kiosk and nutritional education (KSEAN);Intervention 2: Optimized physical activity (AFSO), where the physical education classes will be taken by a specialized physical education teacher or a primary teacher with a specialization in physical education. The effective class time will be a minimum of 70 min, during which half of the time should involve undertaking activities of moderate to vigorous intensity;Intervention 3: Healthy kiosk and nutritional education (KSEAN) + Optimized physical activity (AFSO);Control group: Physical education classes will follow the curriculum as indicated for the subject of physical education and health (AFS).

The study will be conducted in 12 clusters (schools) in three regions of Chile (VIII, VI and Metropolitan), distributed in four schools per region, randomly assigned to KSEAN, AFSO, KSEAN+ AFSO or control.

#### Study hypotheses

Integrating school-based interventions over a period of two school years that cover nutritional education, along with the implementation of a healthy kiosk and 4 h per week of physical education classes, where 50% of the time involves physical activity of moderate to vigorous intensity, is more effective in controlling obesity in children between 6 and 10 years of age than implementing each of these interventions separately.

Incorporating nutritional education into the curriculum, where the dietary message provided in the “Chilean Dietary Guidelines” [27] published in 2012 is conveyed, along with the implementation of healthy kiosks at schools, improves the dietary knowledge and behaviours of children between 6 and 10 years of age and guides them to choose foods low in calories inside schools, thereby helping to manage the increase in childhood obesity.

Optimized physical education and health classes, i.e. those undertaken by a specialized physical education teacher, with a total duration of 4 hours per week in separate blocks, where 50% of the effective class time involves conducting activities of moderate to vigorous intensity designed to improve the fitness levels of children aged between 6 and 10 years, helps in managing the increase in childhood obesity.

### Cluster inclusion criteria

The inclusion criteria included:Primary public schools located within the Metropolitan Region, Region VI and Region VIII of Chile.Schools that are classed with a high school Vulnerability Index by JUNAEB (IVE ≥ 60 JUNAEB) [28].Schools that have not been included in previous interventions with programmes that promote healthy lifestyles.Full-time co-educational schools with a minimum of 600 students.Schools that have specialized physical education teachers.

### Participant inclusion criteria

Students attending public primary schools regularly between the ages of six and ten.

### Participant exclusion criteria

Children excluded from physical education classes due to medical reasons.

#### Recruitment of school (clusters)

For the purpose of this effectiveness study, all of the information regarding public schools was made available to the municipal education departments. This did not require any additional effort or resources for the purpose of recruitment.

From a total of 71 full-time public primary schools within the three regions previously indicated (17 in the Metropolitan Region, 29 in Region VI and 25 in Region VIII), schools with an IVE ≤ 60 were excluded, leaving a total of 58 schools available. Then schools that had previously undergone intervention as part of healthy lifestyle programmes were also excluded, leaving 45 schools, of which only 28 were co-educational and had more than 600 students between 6 and 10 years of age.

Teaching staff qualifications at each school were reviewed and only 18 schools had specialized physical education teachers (six in the Metropolitan Region, eight in Region VI and six in Region VIII). From these 18 schools, four schools per region were chosen at random.

#### Recruitment of participants

Selection of potential participants for each intervention mode and for the control group is to be conducted after randomly selecting the four schools per region.

Meetings are to be held with representatives from the education board and the principals from the participating schools to explain in detail the stages of this research study and the activities that will be undertaken. Afterwards, each school is to invite the parents of the potential participants to meet with the research team, who will explain in detail the aim of the research study. The parents will also be provided with an information sheet detailing the nature and importance of this study and indicating explicitly that it is necessary to have the parents’/guardians’ consent before a child can participate in this study.

A phone number will also be provided to the parents to use in case of any doubts or concerns related to this study. The children will be invited to participate in the project at this time. All parents that indicate that they do not want to participate will be thanked for their time and cooperation.

Children older than 8 years of age that are motivated to participate will be invited to sign an agreement, which will later be used to inform the parents and invite them to participate by signing the consent form. Both the agreement and the consent form have been previously approved by the ethics committee of the Nutrition and Food Technology Institute (INTA) from the Universidad de Chile.

Once the consent forms have been signed, a third meeting is to be organized, where the activities related to this study to be conducted during the school year will be described in detail.

Parents will be informed that this study will determine the nutritional status of each child by measuring weight, height, skinfolds and waistline. These measurements only require that the children remove their shoes and any other heavy element that they might be carrying. It will also be indicated that they will need to answer a survey aimed at determining their current dietary behaviours and that the children’s fitness levels, along with the intensity of the activities conducted in the physical education classes, will be determined by conducting the following tests:Grip strength: consists of squeezing a dynamometer with both right and left hands. This instrument measures the grip strength of the child [29].Measuring the distance of a jump done with both feet together and without a run-up [29].Measuring the intensity of the physical activity by using a pedometer [30], which is a portable device used to count steps that will be placed on the waist of children and secured with a belt while they participate in the physical education classes.

It will be indicated to the parents that all of these tests will be conducted under the supervision of a qualified physical education teacher with experience in conducting all of the tests along with a teacher from the school. It will also be explained that all of the tests should take approximately 15 min to complete and that these will be conducted at the beginning and end of the school year during class time. The only measurement that will be taken throughout the whole year is the intensity of the physical education class. The child’s nutritional status will be informed by means of a letter addressed to the parents.

It will also be indicated that the participation in this study is voluntary and that a child can choose to stop participating at any moment. Additionally, it will be made clear that the participation in this study will not incur any cost for the families of the children nor the school, and that all of the information collected will be kept confidential and will only be used for this study.

The diagram shown in Fig. 1 below, shows the flow of the suggested recruitment process for this study:

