Each component of the intervention modes is described below:Nutritional Education Intervention: This intervention is based on the “Social Cognitive Learning Theory”, which incorporates the interdependency relationship between personal characteristics, behavioural factors and environmental influences [31]. Teachers will provide knowledge and skills in relation to choosing healthy foods at school and at home by providing learning material. Year one to year four students participating in the programme will work with learning material based on the dietary guidelines for the Chilean population that provides nutritional concepts that are reinforced with theory and practical activity, along with the creation of healthy messages [32]. To enhance the effectiveness, the nutritional education activities will be scheduled over 16 sessions of 90 min each. As this is not part of the curriculum, the teacher in charge of each teaching unit (UTP), at each individual school, will define the time when this content will be presented to the students. The implementation of the learning material, including teacher interviews and display of the work conducted by the children in wall displays, will be supervised by a nutritionist, who is part of the research team.Healthy Kiosk Implementation: The model described by Bustos and colleagues in the *Manual de Implementación de un Espacio y Punto de Venta Saludable en Escuelas Básicas de Chile* [33] will be replicated in this study. This considers the following:The construction of a Healthy Space, located within the school. This space is defined as a place that will encourage healthy lifestyles by promoting recreational activities, the sale of healthy foods and the implementation of various educational strategies aimed at modifying and strengthening healthy behaviour amongst schoolchildren. The Healthy Space will consist of a healthy kiosk, surrounded by tables, chairs and a number of games of an attractive design and painted in bright colours. The kiosk will be built in accordance with what is established in the “Reglamento Sanitario de los Alimentos” [34] and its design will promote the visibility of the food that will be displayed in refrigerated display cases and shelves inside the kiosk.The food offering will consist of avocado and fresh cheese or tomato sandwiches, fat-free yoghurt and milk, milk-based desserts, jelly, sugar-free biscuits, cereals, fresh and dried fruits, sugar-free juices and drinks, mineral water and other snacks low in calories. Processed foods will be determined to be low in calories if the nutritional information on the packaging shows the portion sizing and the nutritional information per portion and if this does not exceed 130 Kcal, 3 g of total fats, 20 g of carbohydrates and 140 mg of sodium. For fruits and vegetables a standard portion of 150 g is considered acceptable, as is 30 g for nuts. Also, it will be established that dairy products must be fat-free or low in fat and that other drinks must be sugar-free [33].Strategies for promoting the sale of healthy foods and processed foods low in calories will be established based on behavioural economics, which places the food recommended by the Chilean Dietary Guidelines, such as fruits, vegetables and dairy products, amongst others, in the most visible place within the kiosk. Alongside this, positive reinforcement statements promoting the benefits of consuming healthy foods will be displayed to promote their sale. Also, the kiosks will be fitted with an information board displaying various themes related to the promotion of a healthy lifestyle and a price list of foods available for purchase.Training will be provided for the kiosk staff in topics such as healthy eating, how to read and understand the nutritional information displayed on food packaging, hygiene, food preparation and handling, and communicational and marketing strategies for promoting the sale of healthy foods.

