Physical Activity Intervention: The optimized physical education classes will consider what is already established in the curriculum for the subject physical education and health, with four teaching hours per week, distributed in blocks of 90 min each on different days of the week. Each school selected for this mode of intervention will have a specialized physical education teacher or a teacher with specific training in physical education. Teachers will receive further training to ensure: 1) that the effective class time has a duration of 70 min; 2) that 50% of the effective time consists of activities that demand a moderate to vigorous intensity. Monitoring will be carried out of all of the physical education classes conducted for years 1 to 4, by external physical education teachers that have been previously trained and standardized. They will measure the effective class time and will select children at random to wear the pedometers during the class.

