##### Optimized physical activity (AFSO) primary dependent variable

Fitness as measured in the lower body by the distance, in centimetres (cm), of a jump done with both feet together and without a run-up, and in the upper body by a dynamometer, which measures the isometric force in kilograms (kg) of the upper body by participants squeezing the instrument with the right and left hand.

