### Data collection

#### Baseline data collection

During the baseline evaluation, participating children will be interviewed by the field personnel, who have been previously trained for this task. The evaluation is to take place at each participating school, following prior authorization by the relevant municipal authorities and school principals.

The following information will be registered.General information about each participant: name, class, gender, RUT (national ID number), and whether the participant receives benefits under the nutritional school programme and/or the social protection programme. These are government programmes that provide benefits to persons, families or territories that are classed as being in a vulnerable situation [37].Anthropometry: weight, height, skinfolds (biceps, triceps, subscapular, suprailiac).Fitness level: dynamometry of right and left hand to measure the isometric strength of the upper body, and length of jump with feet together to measure the explosive strength of the lower body.Duration of moderate to vigorous physical activity during physical education classes.A report of the nutritional knowledge and habits regarding the consumption of dairy products, fruits, vegetables, water, legumes, fish and snacks.A report detailing the main types of food purchased at the school kiosk and the amount of money spent.Food offering at the school kiosk: identification of the types of food and their macronutrient contribution.Number of street food carts/stalls that can be found outside the school and their distance in metres from the main school access.

All of the above evaluations will also be conducted after 8 months of intervention (before starting the summer holidays), after 12 months of intervention (return from summer holidays) and after 20 months of intervention (at the end of the second school year).

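### A teacher from each school, who can be expected to know the arm, co-supervises the effort-dependent jump and grip tests that form the primary variable for optimized physical activity (AFSO)

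*Protocol article*

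**What the plan says.** All references are to the protocol article.

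- **Who supervises.** Recruitment of participants lists grip strength, standing jump and pedometer measurement. It says parents will be told that all of these are conducted "under the supervision of a qualified physical education teacher with experience in conducting all of the tests along with a teacher from the school".
- **What the tests are for.** Under Outcome measures, the AFSO primary dependent variable is "Fitness as measured in the lower body by the distance, in centimetres (cm), of a jump done with both feet together and without a run-up", together with right- and left-hand dynamometer force.
- **Unit of allocation.** Under Design, the 12 schools are "distributed in four schools per region, randomly assigned to KSEAN, AFSO, KSEAN+ AFSO or control".
- **Who delivers the interventions.** The detailed description of the intervention modes gives school teachers this role. For nutrition education, "Teachers will provide knowledge and skills in relation to choosing healthy foods at school and at home by providing learning material". For AFSO, "Teachers will receive further training to ensure: 1) that the effective class time has a duration of 70 min".
- **Other staff.** Physical education classes are monitored "by external physical education teachers that have been previously trained and standardized". At the evaluations, "participating children will be interviewed by the field personnel, who have been previously trained for this task".
- **Controls.** The Control group section gives control schools the same evaluations as the intervention schools.

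**The concern.** Jump distance and grip force in children aged 6 to 10 depend on how the task is explained and how strongly the child is urged on. One of the two supervising adults is on the staff of the school being tested. That school has a single allocation, and the kiosk, the classroom sessions and the retraining of physical education teachers make it visible. The teacher may also want the school's programme to do well.

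If such teachers encourage children more in AFSO schools than in control schools, and the difference arises or grows after baseline, the extra centimetres or kilograms would be counted as a treatment effect on the AFSO primary variable. The analysis cannot separate this from a true gain in fitness, because each supervising teacher appears in only one school and so in only one arm. A mixed model that respects clustering widens the interval but does not remove a systematic shift between arms.

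**Working it through.** **The plan's own figure.** Determination of sample size gives 130 subjects per cluster for grip strength and a total of 1560. The total is correct: 130 × 12 = 1560. The 130 itself cannot be reproduced, because the section gives a 20% improvement but no mean, SD or intracluster correlation for grip. The point here does not depend on that figure being right.

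**Does the supervising teacher belong to an arm?**

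1. Schools are randomised, one per arm in each of three regions, so 12 / 4 = 3 schools per arm (Design).
2. A teacher from the school therefore belongs to that school's arm.
3. Teachers at intervention schools are trained for or deliver the programme (detailed description of the intervention modes), so knowledge of the allocation can be expected.
4. The tests under this supervision include jump and grip (Recruitment of participants), which are the AFSO primary variable (Outcome measures).

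The link from supervisor to arm thus holds for the school's own teacher. It is not shown for the lead physical education teacher.

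**What would a shift do? (illustration only)**

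Inputs:
- children per arm: 3 × 130 = 390, from the stated 130 per cluster;
- two-sided test at 5%, AFSO against control, normal approximation;
- no clustering and no baseline adjustment (assumed);
- no true effect, and a shift b in favour of AFSO of 0.05 or 0.10 SD (assumed; the article gives no such figure).

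Standard error of the difference, in SD units: SE = √(2/390) = 0.0716.

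False-positive rate: P = 1 − Φ(1.96 − b/SE) + Φ(−1.96 − b/SE).

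| Shift b (SD) | b/SE | False-positive rate |
|---|---|---|
| 0 | 0 | 5% |
| 0.05 | 0.70 | 10.7% |
| 0.10 | 1.40 | 28.7% |

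The estimate itself would be biased by the full b in each case. Applying the clustering coefficient of 0.00012, which the article states for BMI z-score, changes the rates only slightly, to 10.7% and 28.3%. A larger intracluster correlation would raise the SE and lower these rates. A baseline-adjusted analysis would lower the SE and raise them for the same post-baseline shift.

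**The case against.** The strongest reply is that the sentence sits in a section on recruitment, reports what parents are told, and speaks only of supervision. A school adult being present while children are tested in class time fits a safeguarding role, and what the fix asks for may already be the practice. Control schools receive the same evaluations. Tester scripts and schedules usually belong in a field manual, which an article need not reproduce.

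Part of this stands. The absence of a blinding statement or a tester manual is not the point, and no misconduct is implied. But the article does state that the school's teacher shares the supervision, and it sets no limit on that role. Equal evaluations in control schools do not help if the arm-aware co-supervisor is a different person in each school.

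A reader might go further in four ways that the documents do not support:

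- **That the tester is tied to the arm.** The lead physical education teacher is not said to be school staff, to stay with one school, or to deliver AFSO.
- **That the school teacher scores the tests, or is the AFSO provider.** The text says neither that this teacher instructs, reads or records, nor which teacher it is.
- **That the external class monitors are kept out of testing.** They handle the pedometers in class, and pedometer measurement is among the tests that the qualified teacher supervises. They may be the same people.
- **That supervisor differences destroy power.** That would require an effect size and SD for grip, which the article does not give; the 0.2 in the sample-size section is for BMI z-score. Stable differences between supervisors would also largely cancel against the baseline measurement at t1.

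**Conclusion.** The point holds as a risk of bias built into a stated arrangement. A school employee who belongs to one arm, and can be expected to know it, co-supervises an effort-dependent primary variable. The exposure is to differential encouragement that arises or grows after baseline; a difference already present and unchanged since t1 would largely drop out.

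The size is unknown. Under the assumptions shown (390 children per arm, no clustering, a shift of 0.05 to 0.10 SD), the false-positive rate of one AFSO-control comparison would be about 11% to 29% instead of 5%. These figures show that a small shift would matter. They do not show that one occurs. No claim about lost power is made, and none about the lead tester being confounded with arm. This is an inexpensive improvement worth making rather than a fault that invalidates the design.

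**What to change.** Reword the supervision sentence under Recruitment of participants, and the matching parent information and field instructions, so that:

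1. the school's teacher is present only to look after the children, and does not instruct, encourage, read or record;
2. the qualified physical education teacher who runs the jump and grip tests comes from outside the school and gives one scripted instruction, with the same wording and the same encouragement in every school;
3. the same tester or team measures all four schools of a region at each time point. Each region holds one school per arm, so tester is then balanced over the four arms.

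The cost is less flexible test dates and some travel between schools. The sample size does not change. A further rule that testers may not score schools whose classes they monitor is not recommended: it could need extra staff or swaps between regions, and the point does not depend on it.
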